## Abstract

**Background:**

Patients in Intensive Care Units (ICU) are often exposed to prolonged immobilization which, in turn, plays an important role in neuromuscular complications. Exercise with a cycle ergometer is a treatment option that can be used to improve the rehabilitation of patients on mechanical ventilation (MV) in order to minimize the harmful effects of immobility.

**Methods/Design:**

A single-blind randomized controlled trial (the MoVe ICU study) will be conducted to evaluate and compare the effects of early rehabilitation using a bedside cycle ergometer with conventional physical therapy on the muscle morphology of the knee extensors and diaphragm in critical ill patients receiving MV. A total of 28 adult patients will be recruited for this study from among those admitted to the intensive care department at the Hospital de Clínicas de Porto Alegre. Eligible patients will be treated with MV from a period of 24 to 48 h, will have spent maximum of 1 week in hospital and will not exhibit any characteristics restricting lower extremity mobility. These subjects will be randomized to receive either conventional physiotherapy or conventional physiotherapy with an additional cycle ergometer intervention. The intervention will be administered passively for 20 min, at 20 revolutions per minute (rpm), once per day, 7 days a week, throughout the time the patients remain on MV. Outcomes will be cross-sectional quadriceps thickness, length of fascicle, pennation angle of fascicles, thickness of vastus lateralis muscle, diaphragm thickness and excursion of critical ICU patients on MV measured with ultrasound.

**Discussion:**

The MoVe-ICU study will be the first randomized controlled trial to test the hypothesis that early rehabilitation with a passive cycle ergometer can preserve the morphology of knee extensors and diaphragm in critical patients on MV in ICUs.

**Trial registration:**

NCT02300662 (25 November 2014).

## Background

Patients in Intensive Care Units (ICU) are often exposed to prolonged immobilization, which can play an important role in neuromuscular complications [1, 2]. Bed rest results in skeletal muscle weakness, progressing to muscle atrophy and losses of 3–11 % of muscle mass during the first 3 weeks of immobility [3]. This loss of muscle mass and muscle weakness, in turn, are the result of acquired myopathy, polyneuropathy or a combination of the two [4]. The prevalence of acquired polyneuropathy among patients in intensive care settings is in the range of 58–96 % [5]. Notwithstanding, recent evidence suggests that muscle weakness can be present within hours of starting mechanical ventilation (MV) and is evident in 25–100 % of patients ventilated for more than 7 days [6]. Among these patients, muscle weakness is associated with increased length of hospital stay and higher mortality and with impaired functional status that can still be detected years after hospital discharge, compromising patients’ quality of life [7, 8].

The combination of prolonged MV and the effects of immobility causes significant changes to muscle fibers, reducing both respiratory and peripheral muscle strength [9]. While this muscle weakness has a multifactorial etiology, early rehabilitation of patients in ICUs can help to keep the atrophy, loss of muscle mass and loss of physical conditioning associated with bed rest to a minimum [2]. One resource that has proved to be of great utility in hospitals is the cycle ergometer, which is a stationary piece of equipment designed to enable cyclical rotations of lower and/or upper extremities and can be used to perform passive, active and resisted exercises [1].

Treatment with the cycle ergometer has been shown to improve quadriceps strength, functional status and 6-min walking results at hospital discharge [10]. Although this therapy is widely used in outpatient settings with the objective of improving rehabilitation of patients with chronic pulmonary disease, few studies have assessed its effects in hospital settings, particularly in ICUs [11, 12].

This article provides a detailed description of the background, target population and methodology of the MoVe-ICU study, an randomized controlled trial (RCT) investigating the effects of early rehabilitation using a bedside cycle ergometer combined with conventional physical therapy versus conventional physical therapy alone on the muscle morphology of the knee extensors and the diaphragm.

## Methods

This study will be financed by the Fundação de Amparo à Pesquisa do Estado do Rio Grande do Sul (FAPERGS) research funding agency and it will be conducted in accordance with the principles laid out in the Helsinki Declaration and with Good Clinical Practice. Procedures will be in accordance with National Health Council (Conselho Nacional de Saúde: resolution number 466/12). The HCPA Ethics Committee has approved the study (CEP HCPA number 10-0530) and informed consent will be obtained in writing from all patients who are taking part.

### Patients

This is a single-blind RCT that is going to be conducted by the intensive care and physiotherapy departments at the Hospital de Clínicas de Porto Alegre (HCPA)–Universidade Federal do Rio Grande do Sul (UFRGS). Patients of both genders aged ≥18 years will be recruited from among those admitted to the HCPA ICU and undergoing MV from 24 to 48 h after transfer from the emergency department or wards, no more than 1 week after admission. Exclusion criteria will include neuromuscular diseases causing motor deficits, such as strokes, multiple sclerosis, amyotrophic lateral sclerosis, myasthenia gravis and Guillain-Barré syndrome. Patients will also be excluded in the event of the following: extubation less than 48 h after enrollment on the study; hemodynamic instability (norepinephrine > 0.5 μg/kg/min for arterial blood pressure > 60 mmHg); complications during the protocol such as pneumothorax, deep vein thrombosis or pulmonary embolism; Shilley catheter in the femoral vein; reintubation; delayed weaning (3 failed spontaneous ventilation tests); body mass index (BMI) > 35 kg/m^2^ [2]; or emergence of eschar in the calcaneus area during the protocol.

For sample selection, an assessor is going to conduct a daily search for potential trial participants using the hospital computer system. Then, electronic medical records will be reviewed by patient identification, medical diagnosis, and current medical condition in order to assess patients for eligibility. The next of kin to each eligible patient will be approached for study enrollment. Those who agreed to participate will be asked about the laterality of the patient and will be required to provide written consent.

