### Interventions

Conventional (chest and motor) physical therapy is going to be performed by staff physical therapists who have at least 2 years of experience in the care of critically ill patients. All patients will receive 30-min physical therapy sessions twice daily (morning and afternoon). The protocol consists of passive diagonal movements based on the proprioceptive neuromuscular facilitation (PNF) stretching technique for the upper and lower extremities (two sets of 10 repetitions per set of each diagonal movement bilaterally) and manual bronchial hygiene techniques, such as chest compression-vibrations, resuscitation maneuvers with an Ambu® bag, Ambu, Ballerup, DK), and suction of secretions when necessary.

The intervention group (IG), in addition to conventional physical therapy, is going to undertake passive cycling exercise training for the lower extremities using a bedside cycle ergometer (Flexmotor; Cajumoro, São Paulo, SP, Brazil). For the cycling exercise, patients will be in the supine position with the head of the bed elevated to 30 °. Each patient will perform passive cycling movements at 20 rpm for 20 min once daily, 7 days a week, in the afternoon prior to conventional physical therapy, until extubation or day 7 of the protocol. The protocol will be discontinued if hemodynamic instability occurs (requiring norepinephrine >0.5 μg/kg/min for a mean arterial pressure (MAP) >60 mmHg), systolic blood pressure (SBP) >200 mmHg, heart rate <40 beats/min and persistent peripheral arterial saturation < 88 % or if performing tracheostomy is required.

Before and after each exercise session, the cycle ergometer will be cleaned following the cleaning procedures adopted in the ICU and the criteria established by the hospital infection control committee. Before starting the cycling exercise, all procedures will be briefly explained to the patient regardless of their level of consciousness or sedation. To minimize contact with the device, the heel region is going to be covered with sterile gauze and secured with adhesive tape so that the ankle joint will be close to a 90 ° angle. The passive cycling movements generate alternating extension and flexion of the knee and hip, bilaterally, for 20 consecutive minutes. All procedures will be performed under the supervision of one of the investigators.

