In the two groups, arterial blood gas values will be recorded daily and the following parameters monitored during all sessions in order to monitor the safety of the technique: heart rate, respiratory rate, MAP, peripheral oxygen saturation, and ventilatory parameters.

After extubation or on day 7 of the protocol (whichever occurred first), all patients willreceive a second ultrasound examination (final assessment) and continue to receive conventional physical therapy until ICU discharge.

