### Randomization

Patients will be randomly assigned to receive either conventional physical therapy (conventional group) or exercise training intervention using a cycle ergometer associated with conventional physical therapy (intervention group). Randomization sequence is going to be created by using the website www.randomization.com, with a 1:1 allocation ratio using blocks of 10 participants.

To ensure the confidentiality of randomization sequence, the sequence will be generated by an assessor who has not participated in data collection or study design and will be contacted by telephone only after the participant has been included in the study and is ready to start the protocol.

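### At least three of the listed exclusions are events that follow randomisation, so randomised patients can be removed for reasons that treatment may influence

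*Protocol article*

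**What the plan says.** All references are to the protocol article.

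- **Patients.** After the neuromuscular diseases the list continues: "Patients will also be excluded in the event of the following: extubation less than 48 h after enrollment on the study". It goes on to "complications during the protocol such as pneumothorax, deep vein thrombosis or pulmonary embolism" and ends with "emergence of eschar in the calcaneus area during the protocol". Between these stand haemodynamic instability, a femoral catheter, a BMI limit and "reintubation; delayed weaning (3 failed spontaneous ventilation tests", with no statement of when they apply.
- **Randomization.** The person holding the sequence "will be contacted by telephone only after the participant has been included in the study and is ready to start the protocol".
- **Interventions.** A separate rule ends treatment: "The protocol will be discontinued if hemodynamic instability occurs", with further criteria. On the ergometer: "To minimize contact with the device, the heel region is going to be covered with sterile gauze". On follow-up, after extubation or on day 7: "whichever occurred first), all patients willreceive a second ultrasound examination (final assessment".
- **Assessment.** The final scan is set for day 7 or 24 h after extubation, whichever is first.
- **Outcomes.** The primary endpoint is the change in quadriceps thickness. Duration of ventilation, successful extubation, length of stay and death are also assessed.

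**The concern.** Randomisation makes the two groups comparable at the moment of the call. A rule that later removes patients because of what happened to them replaces the randomised groups with selected ones. If the event depends on both prognosis and arm, the difference in muscle thickness mixes the effect of cycling with the effect of selection.

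Two features make this more than a formality. First, early extubation leads to exclusion while duration of ventilation and successful extubation are outcomes, so patients are selected on something close to what is being measured. Second, the heel touches the ergometer only in the cycling arm, and the Interventions section covers it to limit that contact; yet a heel eschar is a ground for exclusion. Heel eschar, thrombosis, embolism and pneumothorax are not named as outcomes or among the safety parameters. The trial could therefore lose information on a possible harm as well as the balance of its primary comparison.

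**Working it through.** **1. Which exclusions follow randomisation?**

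| Item in Patients | Dated by the text? | Reading |
|---|---|---|
| Extubation under 48 h after enrolment | Yes | After randomisation |
| Pneumothorax, deep vein thrombosis, pulmonary embolism | Yes, during the protocol | After randomisation |
| Heel eschar | Yes, during the protocol | After randomisation |
| Reintubation; delayed weaning | No | Either |
| Haemodynamic instability | No; also a stopping rule in Interventions | Either |
| BMI; femoral catheter | No | Can be read as baseline |

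The first three follow because the call is made when the patient is ready to start the protocol.

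**2. Does excluded just mean that cycling stops?** Interventions has its own rule for discontinuing the protocol. Patients uses a different verb, under exclusion criteria, and lists haemodynamic instability a second time. The natural reading is that an excluded patient leaves the study. Against that, Interventions promises the final scan to all patients, and a patient extubated early has a scan scheduled under Assessment. The sections do not settle the matter, and no passage keeps excluded patients in the analysis.

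**3. The plan's own figure.** Inputs from Sample size calculation: effect 1.2 (printed as standard errors; it reproduces when read as SD), 5 % level (two-sided assumed), power 85 %. A two-sample t-test needs 13.50, rounded up to 14 per group, with power 86.3 % at 14. The stated 14 is reproduced with nothing added for exclusions. One patient is 1/28 = 3.6 % of the sample.

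**4. Loss of precision.** The documents give no exclusion rate, so a range is assumed, equal in both arms:

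| Excluded | Left per group | Power at 1.2 SD |
|---|---|---|
| 10 % | 12.6 | 82 % |
| 20 % | 11.2 | 77 % |
| 30 % | 9.8 | 71 % |
| 40 % | 8.4 | 63 % |

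**5. Bias, as an illustration.** Assume no true effect, a standard normal severity score with correlation r to muscle loss, and removal of the most severe fraction p of an arm. The mean severity of those left falls by φ(z)/(1 − p), where z is the upper-p normal quantile.

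- p = 0.10: 0.1755/0.90 = 0.195
- p = 0.25: 0.3178/0.75 = 0.424
- p = 0.30: 0.3477/0.70 = 0.497

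Bias = r × (difference between arms), with 10 % removed from control and more from cycling:

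| Cycling arm | r = 0.5 | r = 0.7 |
|---|---|---|
| 25 % | 0.5 × 0.229 = 0.11 SD | 0.7 × 0.229 = 0.16 SD |
| 30 % | 0.5 × 0.302 = 0.15 SD | 0.7 × 0.302 = 0.21 SD |

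Here the bias favours cycling. If the least severe are removed instead, as early extubation plausibly does, the same sum gives the opposite sign. Equal fractions under the same rule give zero. For scale, the standard error of the difference with 14 per group is √(2/14) = 0.38 SD.

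**The case against.** **Several stronger readings are tempting, and the text does not carry them.**

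- A reader might infer that every item in the list is an exclusion after randomisation. Reintubation and failed weaning carry no such wording and sit beside baseline criteria. Patients may enter up to a week after admission, so a reintubation could precede enrolment. These items are ambiguous.
- A reader might infer from the place of the stopping rule, in the cycling paragraph, that events are detected differently by arm. But the exclusions in Patients name no arm, Interventions monitors both groups in all sessions, and the word protocol is also used there for conventional therapy. What remains is one extra session a day in the cycling arm, which does not show unequal detection.
- A reader might infer that harms are bound to vanish from the results. No passage says that excluded patients go unreported. A participant flow chart or adverse-event table may stand in a fuller document that is not shown. Only the absence of these events from the named outcomes and safety parameters can be stated.
- The article does not say that the heel covering is meant to prevent eschar, and its Discussion links pressure sores to delayed weaning, which can occur in either arm. A link to the device is possible, not established.

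**The size is not evidence.** The rates and correlations are invented for illustration. The largest figure, 0.21 SD, is 0.21/0.38 = 0.56 of one standard error and is small beside a planned effect of 1.2.

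All of this stands, and it narrows the point without removing it. An article may leave analysis sets to another document, but this one states an exclusion rule, and that rule acts on randomised patients.

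**Conclusion.** The concern holds for the three dated events and possibly for the three undated ones. As written, randomised patients can be removed for events that treatment may influence and that partly coincide with the trial's outcomes. The direction of any bias is open. Its size is unknown: about 0.1–0.2 SD under the assumed unequal removal, and nil if removal is equal under the same severity rule. The case rests on the principle and on the stated rule, not on these figures. It should be put right because the correction is specific, restores the randomised comparison and mostly uses scans that the article already schedules. More recruitment would restore power but would leave the selection in place.

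**What to change.** 1. In Patients, limit the exclusion criteria to conditions checked before the randomisation call, and date the items that are now undated.
2. Keep every randomised patient in follow-up, with the final scan already planned for all patients in Interventions and Assessment, and analyse each in the allocated group.
3. Report heel eschar, thrombosis, embolism, pneumothorax and haemodynamic instability by arm.
4. Keep the reduced set only as a labelled sensitivity analysis.
5. Reconcile Patients with Interventions on whether a patient with such an event leaves the trial or only stops the protocol. This needs no change to any clinical stopping rule.

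**Cost.** There is wording to change and a few scans to obtain in patients who would now be dropped. Retaining patients who cycled little dilutes the effect. At worst, if a fraction f of the cycling arm had no benefit at all, the expected difference is 1.2 × (1 − f): 1.08 at 10 %, with t-test power of about 79 % at 14 per group, and 0.84 at 30 %, with about 57 %. These fractions are assumed. Recruitment has run since May 2013 (Trial status), so patients already excluded may have no final scan. They should still be counted by arm and reason, and the missing scans acknowledged.

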### Interventions

Conventional (chest and motor) physical therapy is going to be performed by staff physical therapists who have at least 2 years of experience in the care of critically ill patients. All patients will receive 30-min physical therapy sessions twice daily (morning and afternoon). The protocol consists of passive diagonal movements based on the proprioceptive neuromuscular facilitation (PNF) stretching technique for the upper and lower extremities (two sets of 10 repetitions per set of each diagonal movement bilaterally) and manual bronchial hygiene techniques, such as chest compression-vibrations, resuscitation maneuvers with an Ambu® bag, Ambu, Ballerup, DK), and suction of secretions when necessary.

The intervention group (IG), in addition to conventional physical therapy, is going to undertake passive cycling exercise training for the lower extremities using a bedside cycle ergometer (Flexmotor; Cajumoro, São Paulo, SP, Brazil). For the cycling exercise, patients will be in the supine position with the head of the bed elevated to 30 °. Each patient will perform passive cycling movements at 20 rpm for 20 min once daily, 7 days a week, in the afternoon prior to conventional physical therapy, until extubation or day 7 of the protocol. The protocol will be discontinued if hemodynamic instability occurs (requiring norepinephrine >0.5 μg/kg/min for a mean arterial pressure (MAP) >60 mmHg), systolic blood pressure (SBP) >200 mmHg, heart rate <40 beats/min and persistent peripheral arterial saturation < 88 % or if performing tracheostomy is required.

Before and after each exercise session, the cycle ergometer will be cleaned following the cleaning procedures adopted in the ICU and the criteria established by the hospital infection control committee. Before starting the cycling exercise, all procedures will be briefly explained to the patient regardless of their level of consciousness or sedation. To minimize contact with the device, the heel region is going to be covered with sterile gauze and secured with adhesive tape so that the ankle joint will be close to a 90 ° angle. The passive cycling movements generate alternating extension and flexion of the knee and hip, bilaterally, for 20 consecutive minutes. All procedures will be performed under the supervision of one of the investigators.

In the two groups, arterial blood gas values will be recorded daily and the following parameters monitored during all sessions in order to monitor the safety of the technique: heart rate, respiratory rate, MAP, peripheral oxygen saturation, and ventilatory parameters.

After extubation or on day 7 of the protocol (whichever occurred first), all patients willreceive a second ultrasound examination (final assessment) and continue to receive conventional physical therapy until ICU discharge.

### Assessment

After completing the period of 24 to 48 h of MV, patients will be enrolled in the study and an ultrasound will be performed to assess the morphology and thickness of the knee extensors (dominant side) and excursion of the diaphragm muscle. The first ultrasound examination will be performed on the first day of patient participation in the study (initial assessment). A second examination will be performed on day 7 of the protocol or 24 h after extubation, whichever occurred first (final assessment). Both assessments will be performed by the same trained examiner, who will be blind to group assignment and data analysis.

With the patient lying supine, real-time B-mode ultrasound scanning will be performed using a 7.5 MHz linear-array transducer (SonoSite, Washington, DC, USA). The probe willbe coated with water-soluble transmission gel to provide acoustic contact without depressing the dermal surface [13]. First, the quadriceps muscle length will be identified and marked on the skin, and its midpoint determined. To ensure that the same region of the muscle will be scanned on subsequent sessions, a map of this region will be recorded and traced on a clear acetate sheet using a permanent marker. Bony prominences and birthmarks will also be included in the map, as well as the probe outline in order to ensure that the probe is held at the same angle relative to the frontal plane during all measurements [13]. Quadriceps muscle thickness will be determined on cross-sectional images by measuring the distance from the outer edge of the femur to the inner edge of the aponeurosis of the upper attachment of the rectus femoris muscle [14].

Ultrasound-based measurements of the vastus lateralis muscle architecture will be made on images obtained at sites corresponding to the points on the muscle belly of highest contractile muscle volume. The muscle length is going to be marked on the skin, its lower two thirds will be determined, and then a point will be marked on the vastus lateralis muscle belly. With the patient lying in the supine position with legs and knees extended, the hip unrotated and the ankle in a neutral position, the ultrasound transducer will be oriented along the axial plane of the vastus lateralis muscle belly. Axial-plane images of the vastus lateralis will then be acquired and muscle architecture parameters, such as fascicle length (FL), fascicle pennation angle (PA), and muscle thickness [15]. Finally, data on FL will be normalized to femur length for each patient.

Ultrasound measurement of the thickness of the diaphragm muscle will be conducted with patients lying in supine position. The probe will be coated in a water-soluble transmission gel to enable acoustic contact without depressing the surface of the skin. The probe will be positioned perpendicular to the diaphragm in the intercostal space over the tenth rib at the anteroaxillary line [16]. For image acquisition the probe will be coated in a water-soluble transmission gel to enable acoustic contact without depressing the surface of the skin. The probe will then be positioned perpendicular to the diaphragm and the image will be acquired for measurement of the thickness at the end of the inspiration [16].

Subjects will be positioned for assessment of diaphragm excursion lying down in the supine position. The probe will be coated in a water-soluble transmission gel to enable acoustic contact without depressing the surface of the skin. The probe will be positioned using the anatomic window for liver analysis between the medioclavicular line and the anterior axillary line, in the cranial direction. The probe will, therefore, be positioned medially, cranially and dorsally in such a way that the ultrasound beam transects the posterior third of the diaphragm [17, 18]. Inspiratory and expiratory diaphragmatic excursion images will be acquired with the ultrasound machine in M-mode. Inspiratory excursion will be defined as the vertical height measured from the base at the start of inspiration to the apex of inclination at the end of inspiration. Expiratory excursion will be defined as the vertical height from the apex of inspiration until the base returns [17, 18].

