### Outcomes

The primary endpoint with respect to the efficacy of passive leg cycle exercise in preserving muscle morphology may be the difference in cross-sectional thickness of the dominant quadriceps muscle from initial to final assessment between groups. Secondary efficacy endpoints may include changes in muscle architecture parameters, such as vastus lateralis fascicle length, PA, muscle thickness, and diaphragm thickness and excursion. We will also assess length of ICU and hospital stay, duration of MV, successful extubation, and incidences of patient death. In addition, septic (requiring vasoactive drugs) and non-septic patients will be compared in terms of primary and secondary outcomes.

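### Diaphragm thickness is read only at end-inspiration although some patients are extubated between scans, so its change mixes muscle morphology with ventilatory state

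*Protocol article*

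**What the plan says.** All references are to the protocol article.

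- **Phase of the reading (Assessment).** For diaphragm thickness, "the image will be acquired for measurement of the thickness at the end of the inspiration". No end-expiratory thickness is described. Inspiratory and expiratory images in M-mode are described only for excursion, at a different probe position.
- **First scan (Assessment).** "After completing the period of 24 to 48 h of MV, patients will be enrolled in the study and an ultrasound will be performed". All patients are therefore ventilated.
- **Last scan (Assessment).** "A second examination will be performed on day 7 of the protocol or 24 h after extubation, whichever occurred first". Interventions words it slightly differently: "After extubation or on day 7 of the protocol (whichever occurred first". The two wordings should be reconciled, but under either one some patients are extubated at the last scan and others are not.
- **Endpoint status (Outcomes).** "Secondary efficacy endpoints may include changes in muscle architecture parameters, such as vastus lateralis fascicle length, PA, muscle thickness, and diaphragm thickness and excursion". The single primary endpoint is quadriceps thickness.
- **Purpose (Abstract, Discussion).** The hypothesis is that passive cycling "can preserve the morphology of knee extensors and diaphragm in critical patients on MV in ICUs".
- **Analysis (Statistical analysis).** GEE is used for intra-group effects, for group and for the septic versus non-septic subgroups. ANCOVA adjusts for factors such as BMI, duration of protocol and duration of MV. Ventilatory state at the scan is not named.

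**The concern.** The diaphragm thickens as it contracts, and its thickness also varies with lung volume. This is a premise of ordinary physiology; the article does not state it. An end-inspiratory reading is therefore resting thickness plus a component that depends on how the breath is driven. Assessment standardises posture and probe placement, but not ventilatory state. For a patient extubated between scans, part of the recorded change may come from the switch from ventilated to spontaneous breathing, even if the muscle is the same.

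What is at stake is the interpretation of one of the two muscle targets in the hypothesis. Extubation is not a neutral background event either. Outcomes says: "We will also assess length of ICU and hospital stay, duration of MV, successful extubation, and incidences of patient death". The trial thus treats extubation and MV duration as things the intervention might change, and the same event decides the state in which the last scan is taken. Excursion, measured over the breath itself, depends on ventilatory state in a similar way.

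**Working it through.** **The plan's own figure.** The only design figure is 14 patients per group, for quadriceps thickness. Reading the effect size of 1.2 in standard-deviation units, with two-sided 5% significance and 85% power, the two-sample t-test needs 13.5 per group, rounded up to 14. The figure reproduces. It says nothing about the diaphragm, for which no effect size, variance or thickening figure is given.

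**Model of the artefact.** Let T be resting thickness, assumed the same at both scans. Let v be fractional thickening at end-inspiration on the ventilator, s the same after extubation, and d = s − v. Let p be the share of an arm extubated by the last scan. Patients still ventilated at the last scan are assumed to thicken by v again.

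- First reading: T(1 + v).
- Last reading: T(1 + s) if extubated, T(1 + v) if still ventilated.
- Apparent mean change in an arm, as % of T: d × p.
- Apparent difference between arms: d × (pI − pC).
- Added between-patient SD: d × √(p(1 − p)).

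The values of d and p below are assumptions; none is in the article.

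| d (% of T) | Spurious within-arm change, p = 50% | Added SD, p = 50% | Arm difference, 50% v 50% | Arm difference, 60% v 40% | Arm difference, 70% v 40% |
|---|---|---|---|---|---|
| 0 | 0 | 0 | 0 | 0 | 0 |
| 10 | 5 | 5 | 0 | 2 | 3 |
| 20 | 10 | 10 | 0 | 4 | 6 |
| 30 | 15 | 15 | 0 | 6 | 9 |

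For example, at d = 20%: 20 × 0.50 = 10; 20 × √(0.5 × 0.5) = 10; 20 × (0.60 − 0.40) = 4; 20 × (0.70 − 0.40) = 6. If d were negative, every shift would change sign.

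**Same calculation relative to the first reading.** With v = 10% and s = 30%, an unchanged muscle reads 1.30/1.10 − 1 = +18.2%; times a 20-point difference in extubated share, this is 3.6 points. With v = 15% and s = 20%, it reads 1.20/1.15 − 1 = +4.3%, giving 0.9 points.

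**Chance imbalance.** With p = 50% and 14 per arm, the standard error of the difference in extubated shares is √(2 × 0.5 × 0.5 / 14) = 0.189. A 60% v 40% split is about one standard error from equality (0.20/0.189 = 1.06), so it could easily occur by chance. Over repeated trials this is noise, not bias. It becomes bias if the intervention itself alters extubation by the last scan.

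**Which analyses are affected.**

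1. Within-group change: shifted by d × p even with equal shares in the arms.
2. Septic versus non-septic: the same difference formula applies, with the two subgroups' shares in place of pI and pC. Randomisation does nothing to balance those shares.
3. Randomised contrast: a common shift cancels. What remains is noise, plus bias only where the shares differ between arms.

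**The case against.** A reader might infer that the change score measures ventilatory state instead of the diaphragm. The documents do not support that. Resting thickness is part of every reading, and patients still on MV at day 7 are ventilated at both scans. Nor can one say that an unchanged muscle will show a gain after extubation. The article does not give ventilator mode, support level or patient effort at either scan, so both direction and size are assumed. Setting an illustrative diaphragm figure beside the 3–11% loss of muscle mass over 3 weeks in the Background would compare different quantities.

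Randomisation is a substantial defence. With equal extubated shares there is no bias between arms, and nothing in the article shows that the shares will differ. This stands for the main contrast, but not for the within-group or septic comparisons.

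The ANCOVA also helps somewhat. The protocol period ends at extubation or day 7, so a duration below 7 days largely marks extubated patients, discontinuations apart. Together with MV duration, this makes state at the last scan mostly recoverable. But both covariates arise after randomisation, MV duration is itself an outcome, and neither is the state at the scan. They are partial proxies, and adjusting for them may remove some of any real effect.

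Finally, the endpoint is secondary, and neither the primary endpoint nor its sample size is touched. That limits the importance of the point without removing it.

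**Conclusion.** The point holds as a limited measurement problem in a secondary endpoint. The change in end-inspiratory thickness mixes diaphragm morphology with ventilatory state and cannot be read as morphology alone. Within-group and septic versus non-septic results are confounded regardless of balance between arms. The randomised contrast loses precision and is biased only if the extubated share differs between arms.

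The size cannot be determined from the documents. Over the assumed range of d from 0 to 30%, the spurious within-arm change at 50% extubated runs from 0 to 15% of resting thickness, and the spurious arm difference at 60% v 40% from 0 to 6 points. This rests on constant resting thickness, unchanged thickening in patients who stay ventilated, and the physiological premise above. It is worth acting on because a better reading is available cheaply.

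**What to change.** - **Thickness.** At both scans, also capture and measure end-expiratory thickness at the same probe site, and make it the diaphragm-thickness endpoint. Keep end-inspiratory thickness as descriptive.
- **State.** Record at each scan whether the patient is ventilated or breathing spontaneously.
- **Excursion.** Interpret it with that state in mind. Keep the comparison by randomised arm, and give any display by state as descriptive only. State at the last scan is a post-randomisation event, so stratifying the main comparison on it would give up the randomised contrast and split 14 per arm into small cells.
- **Timing.** Reconcile the wording on the last scan between Interventions and Assessment.

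**Cost.** One extra frame and caliper reading per scan, one recorded item, and revised assessment wording. Recruitment has been under way since May 2013 (Trial status), so patients already enrolled whose stored images do not include expiration will have no end-expiratory baseline. Their number should be reported. Treatment, the primary endpoint and the sample size do not change.
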